## Abstract

**Background:**

Chronic pain affects over 30% of the global population and remains a major public health issue due to limited treatment efficacy and the need for mechanism-based, personalized approaches. Motor behavior is theorized to play a role in pain persistence through altered movement patterns, muscle recruitment, and proprioception. While motor behavior is linked to chronic pain, empirical evidence on underlying mechanisms, particularly cortical dynamics, remains scarce.

**Objective:**

This study aimed to investigate longitudinal changes in cortical sensorimotor excitability and their relationship with maladaptive motor behaviors.

**Methods:**

This prospective longitudinal study will follow 150 healthy participants, aged 18‐65 years, recruited from the community, experiencing experimentally induced muscle pain across 4 visits (day 0, day +2, day +4, and 5 days after pain resolution). Pain will be induced using intramuscular injections of nerve growth factor into the extensor carpi radialis brevis muscle. The primary outcome is motor variability assessed during multidimensional wrist movement tasks, and quantified using root-mean-square deviation and muscle synergies (derived from electromyographic recordings of 4 forearm muscles). Secondary outcomes include cortical mechanisms (electroencephalographic peak alpha frequency, transcranial magnetic stimulation mapping, short-interval intracortical inhibition, and intracortical facilitation), sensorimotor integration (evoked potential), cognitive control (multisource interference task), and endogenous pain modulation (conditioned pain modulation). Self-report questionnaires will assess pain intensity and disability (Patient-Rated Tennis Elbow Evaluation, McGill Pain Questionnaire–Short Form, and Likert Muscle Soreness Scale) as well as psychological factors such as fear of movement, pain-related beliefs, and coping strategies (Tampa Scale for Kinesiophobia, Pain Beliefs Questionnaire, and Coping Strategies Questionnaire–Revised). This sample size provides 80% power at 5% significance to detect a medium effect size across 23 predictor variables, with Bonferroni correction and 10% loss-to-follow-up allowance. Data will be analyzed using 2-level growth curve modeling to characterize interindividual differences in motor behavior, cortical dynamics, and pain processing trajectories.

**Results:**

All study procedures have been approved by the Western University Health Science Research Ethics Board (review reference 2025-125757-103291). Funding was provided by the Canadian Institutes of Health Research under grant number 517783 for the period 2024‐2029. Recruitment for the study began in April 2025, and all data collection is expected to be completed by 2028. As of April 2026, we have enrolled 26 participants. Results are expected to be published at the end of 2028.

**Conclusions:**

The findings will advance understanding of motor behavior in pain and lay the foundation for personalized therapies, moving beyond current generic treatments that offer limited benefits.

## Introduction

Chronic pain affects at least 30% of people worldwide [1] and represents a growing public health crisis. Despite its substantial impact, effective treatment remains limited, in part because most interventions rely on standardized, symptom-based approaches that fail to address the diverse mechanisms driving pain across individuals. To advance pain care, a precision approach is needed, one that targets the right mechanism, at the right time, and in the right person.

One mechanism through which pain impacts individuals is motor behavior, a dynamic and adaptive system aimed at minimizing further harm and tightly linked to both the experience and persistence of pain [2]. In the short term, protective strategies, such as reducing movement amplitude or speed, help avoid pain provocation, prevent injury, and promote healing [3]. However, when maintained beyond the acute phase, these behaviors may become maladaptive, leading to stereotyped movement patterns, reduced muscle recruitment variability, increased cocontraction, altered tissue loading, and diminished proprioceptive feedback [2,4-7]. Over time, these changes are thought to produce mechanical, physiological, and neurological consequences that sustain pain. While the link between maladaptive motor behavior and persistent pain is widely acknowledged, empirical data on the underlying mechanisms remain limited. Cortical mechanisms may provide a key link between motor adaptation and persistent pain. Indeed, pain-related changes in corticomotor function can limit adaptive control of movement, favoring protective but inefficient strategies that may contribute to pain persistence [8].

Emerging evidence suggests that cortical mechanisms, particularly changes in sensorimotor cortex excitability and integration, may underpin the relationship between motor adaptation and pain [9-11]. On one hand, in the acute phase, reduced corticomotor excitability appears to serve as an adaptive strategy to protect the painful area and facilitate recovery [9]. However, if these reductions persist, they may impair motor learning and promote rigid, maladaptive movement patterns [12-14], increasing the risk of chronic pain [15,16]. Preliminary experimental data support this dual role [17], highlighting the need for further research to clarify how cortical dynamics interact with motor behavior across the transition from acute to chronic pain. On the other hand, sensorimotor integration, the process by which the central nervous system transforms sensory inputs into motor commands, is disrupted in persistent pain and may contribute to pain amplification [18,19]. While impairments in sensorimotor integration have been demonstrated in clinical pain conditions, evidence linking these changes to motor behavior remains limited [20,21]. Previous work showed that reduced sensorimotor integration is associated with decreased corticomotor output following a noxious stimulus [22]. However, how these alterations influence motor behavior over time, both within and between individuals, and how they interact with other cortical mechanisms, is still poorly understood.

While recent theories propose that cortical changes drive motor adaptations in pain, evidence remains mostly cross-sectional and focused on isolated mechanisms [2,5]. Progress is limited by the lack of human models inducing sustained, functionally relevant muscle pain, restricting the ability to track cortical and behavioral changes over time. This gap hampers our understanding of how pain-related motor adaptations develop and resolve, underscoring the need for longitudinal research to guide personalized pain management.

Here, we outline the experimental protocol and statistical analysis plan to examine individual differences in motor behavior (multidimensional movement task and muscular synergies), cortical mechanisms (corticomotor excitability, peak alpha frequency (PAF), and intracortical inhibition and facilitation), sensorimotor integration (sensory-evoked potentials [SEPs]), cognitive function (multisource interference task [MSIT] and questionnaires), and pain modulation (conditioned pain modulation [CPM]) in response to the progressive development, persistence, and resolution of clinically relevant elbow pain (intramuscular injection of nerve growth factor [NGF] into the extensor carpi radialis brevis [ECRB] muscle). We hypothesize that individuals with low sensorimotor cortex excitability, higher intracortical inhibition, reduced sensorimotor integration, central sensitization, and a passive cognitive response strategy will have less variable motor behaviors and more severe, longer-lasting pain.

## Methods

### Study Design

A prospective longitudinal experimental study will be conducted to follow healthy individuals from the first induction of pain (day 0), as it develops and is sustained (day +2 and day +4), until 5 days after complete resolution of pain (Figure 1). Ethical approval has been obtained from the University of Western Ontario (reference 2025-125757-103291, January 9, 2025).

**Figure 1. F1:**
[figure not shown]
Study timeline. CPM, conditioned pain modulationConditioned Pain Modulation; PRTEE, Patient Rated Tennis Elbow Evaluation; TSK-13, Tampa Scale for Kinesiophobia - ––13 items; PBQ, Pain Beliefs Questionnaire; CSQ-R, Coping Strategies Questionnaire – –Revised; ICF: intracortical facilitation; LMSS, Likert Muscle Soreness Scale; MPQ-SF, McGill Pain Questionnaire - –Short Form; NGF, nerve growth factor; MSIT, Multisource Interference Task; NGF, nerve growth factor; PAF: peak alpha frequency; PBQ, Pain Beliefs Questionnaire; PRTEE, Patient-Rated Tennis Elbow Evaluation; SEP, sensory -evoked potentialsSensory Evoked Potentials; SICI: short-interval intracortical inhibition; TMS, Transcranial Magnetic Stimulation; TSK-13, Tampa Scale for Kinesiophobia–13 items.

### Participants and Inclusion and Exclusion Criteria

A total of 150 healthy, pain-free individuals aged 18-65 years will be included in the study. Each participant will be asked to refrain from consumption of tobacco [23], caffeine [24], and recreational substances at least 2 hours before data collection [25], and short-acting analgesics (eg, acetaminophen) at least 6 hours before data collection [26], so as not to interfere with the perception of pain. Individuals presenting with a history of other major disorders, psychiatric conditions, or contraindications to the use of transcranial magnetic stimulation (TMS) will be excluded. Only right-handed people will be included due to the device used to analyze motor variability, which is custom built for right-handed individuals, and the presence of differences in sensorimotor integration [27] that would influence consistency and increase variability. Participants will be recruited from the community using newspaper or online advertisements and social media sites such as Facebook. Testing will take place at the Western Interdisciplinary Research Building on the University of Western Ontario campus at London (Ontario, Canada). Participants shall receive financial compensation for their participation.

### Data Collection Procedures

#### Primary Outcomes: Motor Behavior

##### Overview

Although a predefined preprocessing pipeline will be applied, data-driven adjustments may be performed when warranted by data quality, statistical assumptions, or artifact structure. Every adjustment will be reported in the final study. Multidimensional movement tasks will be performed to assess both kinematic and muscle synergy variability. Participants will be seated on an adjustable seat with their right forearm resting on a table in neutral pronation-supination with approximately 70° of shoulder abduction. Their wrist will be positioned at the edge of the table with their hand extending beyond it, allowing the forearm to be supported without hindering wrist mobility. The task involves executing multidimensional wrist movements toward 9 white round targets (4.5 cm in diameter), 1 central and 8 peripheral, arranged in a circular configuration, separated by 45° from the central target, at a 1-meter distance on a black fabric wall. The 8 peripheral targets will be separated from the central one according to the functional ranges of motion of the wrist joint [28-31]. The targets will be arranged at 40° flexion (50% of the average amplitude of approximately 80°), or 84 cm below the central target; at 40° extension (57% of the average amplitude of approximately 70°), or 84 cm above the central target; at 15° radial inclination or abduction (75% of the average amplitude approximately 20°), or 27 cm to the left of the central target; and at 20° ulnar inclination or adduction (67% of the average amplitude approximately 30°), or 36 cm to the right of the central target. A green laser pointer, mounted on the dorsal surface of the right hand via an adjustable glove and aligned with the middle finger, will project a laser dot to indicate movement direction to participants. Participants will move the right wrist, keeping the elbow and forearm fixed by hook-and-loop fasteners on the table, to guide the laser pointer from the central target to each peripheral target and then returning to the central target (Figure 2). Movements will be performed in both clockwise and counterclockwise directions, alternating between the two. Each direction will be repeated 3 times, resulting in a total of 6 complete tours. Each tour consists of 16 movements, or 8 round trips from the central target to the 8 peripheral targets, with brief pauses between sequences. The task will follow a metronome cadence of 90 beats per minute, resulting in a total of 96 movements completed in 1 minute and 4 seconds, excluding pauses. Participants will be instructed to prioritize accuracy, aiming the laser pointer precisely at the targets and avoiding any corrective adjustments once a target has been reached. To establish a stable baseline for task performance, participants will undergo a separate familiarization time for all visits, just before the actual task. During this time, they will practice the task until they achieve a performance plateau, defined as a movement accuracy exceeding 95%. Previous research has demonstrated that 3 complete tours (or 48 trials) are sufficient to reach this plateau and that movement accuracy remains stable over several days [32]. Kinematic data will be recorded using a 3D Optotrak motion capture system (Northern Digital Inc) at a sampling frequency of 100 Hz tracking 3 infrared light-emitting diodes bound to the glove on the back of the right hand, roughly matching the distal end of the second and fifth metacarpal bones. Data will be processed by a customized Python (Python Software Foundation) script.

**Figure 2. F2:**
[figure not shown]
Experimental setup for the multidimensional wrist movement task. A laser pointer mounted on the dorsal surface of the glove will be used to reach 1 central and 8 peripheral targets, while the forearm will be secured to restrict movement to the wrist.

##### Kinematic Variability

Kinematic variability of the movement will be quantified each visit using the root-mean-square deviation (RMSD) of the 3D hand movement [33,34] around its mean trajectory. Hand position will first be defined across frames from raw position signals as the barycenter of all 3 active markers rigidly bound to the hand. Marker positions will, however, be low-pass filtered (zero-phase Butterworth filter, fourth order, cutoff frequency to be determined from the power spectrum density of actual data as described in Carbonneau et al [35]) before computing hand velocity as the symmetric derivative of their barycenter. The highest appropriate cutoff frequency across all participants will be applied to all so that no useful signal is lost and all participants’ data follow the same preprocessing. Filtering attenuates the noise amplification inherent to numerical differentiation, reducing spurious velocity spikes that could affect data segmentation. This approach avoids bias by ensuring that preprocessing decisions are not made separately for different visits or pain states and therefore cannot systematically favor one condition over another but could introduce some noise into a certain dataset.

Hand position data will first be roughly segmented into its 16 individual movements based on metronome beats. Finer movement onset and offset will then be defined as the time points at which the tangential velocity of the hand crosses a threshold of 10% of its peak value [36] and then remains beyond it (eg, sustained duration ≥50 ms), preventing transient velocity spikes to be misclassified as movement onset or offset. Trials in which the root-mean-square velocity during the presumed stationary phase exceeds a noise floor criterion (eg,>2% of peak velocity) will be automatically flagged as having irregular baseline activity for the eventual manual validation of the segmentation of all trials. This hierarchical, criterion-based approach minimizes segmentation errors that could artificially inflate RMSD estimates, while substantially reducing the proportion of trials requiring manual segmentation. Each kinematic segment will then be time-normalized to 100 data points.

For each visit, all 6 repetitions (3 clockwise turns and 3 counterclockwise turns) of the same movement will be averaged. The RMSD of concatenated individual hand trajectories relative to their own mean trajectory over the same visit will then be computed. This single scalar index of intravisit kinematic variability will then be entered into growth curve models to characterize longitudinal changes in movement dispersion across the 4 repeated visits independently of end point accuracy.

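### The kinematic main outcome is a linear RMSD of a wrist rotation, so it scales with wrist-to-marker distance; dividing by that distance would remove avoidable noise and a hand-size component from the sex effect

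*Protocol article*

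**What the plan says.** All references are to the protocol article.

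- **Task (Primary Outcomes: Motor Behavior, Overview).** Targets are set as wrist angles and converted to positions "at a 1-meter distance on a black fabric wall". For flexion: "The targets will be arranged at 40° flexion (50% of the average amplitude of approximately 80°), or 84 cm below the central target". For extension: "at 40° extension (57% of the average amplitude of approximately 70°), or 84 cm above the central target". The 15° radial target is placed "or 27 cm to the left of the central target" and the 20° ulnar target "or 36 cm to the right of the central target". Participants move the wrist while "keeping the elbow and forearm fixed by hook-and-loop fasteners on the table".
- **Markers (same section).** Three diodes are "bound to the glove on the back of the right hand, roughly matching the distal end of the second and fifth metacarpal bones". The glove is adjustable.
- **Outcome (Kinematic Variability).** Hand position is the "barycenter of all 3 active markers rigidly bound to the hand". Each movement is resampled to 100 time points. RMSD is taken around the participant's own mean trajectory for that visit, and the resulting scalar goes into the growth curve model. No spatial scaling is stated.
- **Other main outcome (Muscle Synergies).** EMG envelopes are divided by their peak within the visit, partly because electrode placement differs between days.
- **Model (Statistical Analysis).** A two-level growth model with participant random effects. Sample Size counts age, sex and gender among the parameters; no hand dimension appears there.

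**The concern.** The task fixes angles, but the outcome is a length. When a rigid hand rotates about the wrist, a given angular deviation moves the barycenter by an amount proportional to its distance from the wrist. Two people with the same angular control but different hands therefore get different RMSD values. One person whose glove sits further forward at one visit gets a different value with no change in motor behavior. Subtracting the visit's own mean trajectory removes offsets but not a multiplicative factor.

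The study aims to explain why some people move less variably and how this changes over visits. A component of the outcome that reflects anatomy or glove position works against both aims. The protocol already deals with the equivalent placement problem for EMG by normalizing within the visit.

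**Working it through.** **1. Is the task angular?** Wall distance = 100 cm × tan(angle).

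| Angle | Computed | Stated |
|---|---|---|
| 40° | 83.9 cm | 84 cm |
| 15° | 26.8 cm | 27 cm |
| 20° | 36.4 cm | 36 cm |

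The stated distances reproduce. If the laser sits 2 to 4 cm dorsal to the wrist axis (assumption), the 40° targets correspond to wrist angles between 39.6° and 40.5°. The required angles are therefore effectively the same for everyone.

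**2. How does RMSD depend on distance?** Position deviation ≈ r × angular deviation in radians, where r is the wrist-to-barycenter distance. The documents do not give r. Assumption: 65 to 95 mm, reference 80 mm. One set of simulated angular trajectories (6 repetitions × 16 movements × 100 points, angular RMSD 2.49°) was projected at several values of r:

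| r | Linear RMSD | Ratio to 80 mm | RMSD / r |
|---|---|---|---|
| 65 mm | 2.80 mm | 0.81 | 0.0431 rad |
| 80 mm | 3.45 mm | 1.00 | 0.0431 rad |
| 95 mm | 4.10 mm | 1.19 | 0.0431 rad |

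The spread is about ±19% for identical angular behavior. After division by r it disappears (0.0431 rad = 2.47°, close to the 2.49° computed directly). With the barycenter 20 mm dorsal to the axis, the ratios become 0.82 and 1.18, so the relation is close to proportional rather than exactly so.

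**3. Glove position.** Assumption: a shift of 5 or 10 mm at r = 80 mm. Simple proportion gives 5/80 = 6.25% and 10/80 = 12.5%. The simulation with the dorsal offset gives 6.1% and 12.1%.

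**4. Change over visits.** The same 20% fall in angular variability, with the dorsal offset, gives −0.57 mm at r = 65 mm and −0.83 mm at r = 95 mm. On the raw scale the slope therefore scales with hand size, as the level does.

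**5. Rough cost between persons.** Read 65 to 95 mm as mean ± 2 SD (assumption): SD = 30/4 = 7.5 mm, CV = 7.5/80 = 9.4%. Take a between-person CV of angular RMSD of 20 to 30% (assumption), independent of r. The share of between-person variance due to r is about 0.094²/(0.094² + 0.20²) = 18%, or 0.094²/(0.094² + 0.30²) = 9%. Correlations with a between-person predictor shrink by 1 − √(1 − 0.18) = 9%, or 1 − √(1 − 0.09) = 5%, before any adjustment for sex.

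**The case against.** **The model already handles hand size.** This stands in part. A participant random intercept takes up much of a stable difference in level. It does not remove the scaling of within-person changes (step 4) or of predictor effects, nor visit-to-visit glove noise. Age and sex may stand in for hand size in part, but any sex effect is then mixed with hand size. Neither statement of the hypotheses concerns sex.

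**No bias is shown.** This stands. A reader might infer that the mechanistic coefficients are biased. That would need hand size to be related to measures such as SICI or map volume after allowing for age and sex, or glove position to differ systematically by visit. The documents show neither.

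**Glove movement is inferred.** This also stands. The wording about rough matching describes anatomical location, not repositioning error, and the laser on the glove must line up with the middle finger, which limits how it sits. The 5 to 10 mm is an assumption.

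**The size is easy to overstate.** Comparing the two ends of an assumed range gives a striking ratio (95/65 = 1.46) that does not describe typical participants. The effect is modest for most of them (step 5).

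**A condensed article may omit the scaling, and processing may be adjusted.** This carries less weight. The article describes the pipeline from raw markers to model input, so this is a stated outcome definition. The allowance for adjustments concerns data quality, statistical assumptions and artifacts; it does not provide for rescaling.

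**Conclusion.** The point holds in limited form. One of the two main outcomes, kinematic RMSD, is nearly proportional to a distance that has nothing to do with motor control. The proportionality follows from the geometry that the protocol states; the sizes (about ±19% between persons, about 6 to 12% per glove shift) rest on assumed distances. The main consequences are avoidable noise, within-person changes that scale with hand size, and a sex effect that cannot be separated from hand size. The documents do not support a claim of bias in the mechanistic coefficients. Nor does the problem reach the synergy metrics, which are correlations and a time lag and do not depend on this distance. It is worth correcting because the correction is cheap, not because it threatens the study.

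**What to change.** Define the kinematic outcome as RMSD divided by the wrist-to-barycenter radius for that visit, with the radius taken from a sphere fitted to that visit's hand positions. The result is an angular RMSD in radians. Keep the linear RMSD as a sensitivity analysis. Hand orientation computed from the markers is an alternative only if the three markers are clearly non-collinear. The protocol locates them only by the second and fifth metacarpals, and if they lie near that line, rotation about it is poorly determined.

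Feasibility was checked by simulating the planned task with assumed distances of 65 to 100 mm, a 5 mm axis offset and 0.3 to 1 mm of forearm shift. The fitted radius had an SD below 1 mm. The spread in RMSD fell from about 1.5-fold to within about 6%.

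The cost is a few lines in the existing Python processing and a sentence in the protocol. The recorded marker positions suffice, so it can be applied to the participants already enrolled (26 as of April 2026). The downsides are a small error in the fitted radius and the assumption of a single fixed center of rotation.
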